**Respondent-driven sampling**
Network size and characteristics, utilized for respondent-driven sampling weighting
**Internet or mobile phone use**
Type of phone, data plan, and frequency of use; loss of plan; and other family members who have access to the phone
**Venue use**
Information on physical venues where participants frequent will be collected; venues will be included to assess overlap between physical and web-based seed networks
**HIV testing and care history**
Frequency of HIV testing in the past year, date of most recent HIV test, and receipt of HIV test results
**HIV continuum**
Self-reporting HIV infection; current engagement in care, including antiretroviral treatment; adherence; and self-reported viral load status
**Knowledge of pre-exposure prophylaxis (PrEP) and postexposure prophylaxis (PEP)**
Knowledge, perception of, and history of PrEP and PEP use
**Sexual matrix module and sexual risk behavior**
Sexual attraction, identity, and behavior; 7-item question HIV Incidence Risk Index for men who have sex with men (MSM) males only [60,61]; information on number of partners and frequency and types of sexual acts; network of the sexual contacts; location of where sexual experiences occurred; and perceived sexual risk for sexually transmitted infections, including risk for HIV
**Health care use**
Health care and services utilization and engagement and trust between the clinician and patient
**Stigma and mental health**
Self-stigma (internalized homo-negativity) and HIV stigma (with consideration of impact on HIV testing and adherence) adapted from Herek et al [62,63]; mental health will include lifetime and recent history of depressive symptoms and anxiety, using the Patient Health Questionnaire-4 [64], post-traumatic stress disorder (Child Post-Traumatic Stress Disorder Symptom Scale) [65], and experiences of discrimination [66]
**Social environment**
Outness Inventory [67]; intimate partner violence, victimization, and perpetration (Safe Dates instrument) [68]; sexual guilt (Revised Mosher Sex-Guilt Scale) [69]; lesbian, gay, bisexual, transgender, and questioning (LGBTQ) victimization [70]; and social context (perceived parental support and religious environment) [71]
**Substance use**
Car, relax, alone, forget, friends, and trouble (CRAFFT) six-item substance use screen and a modified Time Line Followback assessing days of use of various substances [72,73]
**Engagement in the lesbian, gay, bisexual, transgender, queer (LGBTQ) community**
Measures of strength of engagement and connection in the LGBTQ community

#### Coach-Based MEI for Youth Living With HIV

The second aim of the protocol is an RCT to examine the efficacy of a mobile-enhanced coach-based intervention to achieve sustained retention and engagement in HIV care among youth living with HIV who are not virally suppressed.

#### Aim 2

##### Study Sample

YBLMSM or YBLTW, recruited into aim 1, who are identified as HIV-positive (previously diagnosed with HIV—self-report of HIV-1 and confirmed viral load, or newly diagnosed—no prior history of HIV and rapid HIV test positive) are invited to participate in the RCT of aim 2 of the study. Additional eligibility includes not virally suppressed; no plan to relocate in the next 18 months; not enrolled in another HIV treatment intervention; and currently own or have access to a cell phone, private tablet, or laptop. Potential participants are provided information about the study, consented, and a blood sample for the viral load is obtained (if no recent viral load within 3 months was documented in the medical chart). Participants with an HIV-1 viral load>200 copies/mL are eligible to participate in aim 2. We aim to recruit 240 YBLMSM or YBLTW living with HIV who are not virally suppressed.

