##### Study Procedures

After enrollment, participants complete a baseline survey and are randomized (1:1) to 1 of 2 study arms: coach-based MEI or SOC. Randomization to the intervention arms is stratified by site; age group, to yield a balanced randomization between younger (aged 15-19 years) and older (aged 20-24 years) age groups; and enrollment site.

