The PUSH study uses a built-in randomization engine adapted from previous studies [89]. The allocation between intervention and control arms is determined randomly by the engine, where each round comprises 2 intervention and 2 control assignments that are linked to the stratification factors of site and age group. Once a round is completed, a new round begins.

Participants are asked to participate in research visits at 0, 3, 6, 9, 12, and 18 months (exit interview). This visit schedule aims to ensure frequent contact and to minimize attrition. Laboratories and study-related activities are described in Table 2. Surveys provided at baseline (Textbox 1) are re-administered at each follow-up with additional questions focused on ART, PrEP, barriers, and facilitators to adherence.

**Table 2 table2:** Study visits and associated laboratory tests.

Tasks	Visits					
	Baseline	3 months	6 months	9 months^a^	12 months	18 months
Complete a survey	✓^b^	✓	✓	✓	✓	Exit interview
Provide blood for HIV-1 RNA viral load testing (aim 2) or HIV-1 antibody testing (aim 3)	✓	✓	✓	—^c^	✓	—
Provide urine for drug testing	✓	✓	✓	—	✓	—
Update locator information	✓	✓	✓	✓	✓	—
Meet with MEI^d^ coach (intervention only)	✓	✓	✓	✓	✓	✓
Medical chart review (research staff only)	✓	✓	✓	✓	✓	✓
Compensation, US $	50	50	50	10 check-in via phone; 25 survey	50	25
Participate in an in-depth interview (selected participants)	✓	—	✓	—	✓	—
Compensation, US $	25	—	25	—	25	—

^a^9-month visit constitutes either a brief phone check-in (5 min) or in-person survey (15 min).

^b^Data collected at this time point.

^c^Data not collected at this time point.

^d^MEI: mobile-enhanced intervention.

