#### Sample Size Considerations

We aim to recruit up to 2000 YBLMSM and YBLTW to be screened for eligibility for aims 2 and 3. We conservatively estimate that 15.00% of the RDS recruited sample will be HIV-infected and not virally suppressed, given an HIV prevalence of 25% to 40% among YBLMSM and YBLTW across the sites and as many as 60% of HIV-infected YBLMSM are undiagnosed [4,9].

We expect a 15.0% loss to follow-up over 1 year in aim 2. Starting with n=240 will yield an effective sample size of 204 individuals in total, or 102 in each group, available for analysis in aim 2. A total estimate of n=200 will be enough to detect an average increase in the viral suppression proportion over the 3 follow-up visits of 16.0% from 24.0% assumed in the control arm to 40.0% in the coached-based MEI arm (odds ratio, OR 2.03), assuming a power of 85.0%. We expect a slightly greater loss to follow-up (20.0% loss to follow-up) in participants in aim 3. Starting with n=225 will yield an effective sample size of 180 individuals in total or 90 in each group. We estimate that a total of 180 participants (90 per group), and assuming a 15.0% average rate on PrEP in the control arm, we can detect an average increase of 14.0% to 29.0% (OR 2.31) with power 85.0%. Lost to follow-up estimates are based on the team’s prior work with this population.

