#### Data Analysis

Aim 1 analyses are descriptive and include baseline characteristics related to sociodemographic characteristics, HIV infection, and sexual behavior of the YBLMSM and YBLTW samples across all sites as well as stratified by site. Descriptive tables with unweighted estimates and Pearson chi-squared tests for significance are used to compare age, web-use and venue attendance, and other characteristics of each recruited seed type.

To compare the efficiency of *seeds* from direct versus indirect seed selection in the recruitment of HIV-positive or at-risk youth, we use the RDS statistical package developed by Schonlau and Liebau [90]. This permits an assessment of the overlap of networks across seed types and across recruitment sites. Efficiency is assessed through recruitment diagnostics, including coupon return rate, homophily, the mean number of recruits, and recruitment depth per seed type. This approach also allows us to assess the time from recruitment activation through the achievement of target sample size and response rates. RDS weights will not be utilized in these analyses, as this aim focuses on descriptive sample proportions rather than producing population-based estimates. We will also examine the networks described by younger (aged 15-19 years) and older (aged 20-24 years) participants recruited from different *seeds* and use similar methods to understand the overlap of age groups across different networks.

The primary outcome for aim 2 is durable viral suppression (HIV viral load<200 copies/mL), and the secondary outcome is retention in HIV care (defined as documented 2 or more follow-up medical visits over 12 months, treated as a dichotomous variable). The primary outcome for aim 3 is self-reported PrEP use over 12 months in PrEP users, and the secondary outcome is self-reported condom use in PrEP nonusers. The overall approach is based on an intention-to-treat analysis with treatment assignment (eg, coached-based MEI vs SOC) being the primary independent variable for all models.

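### Aim 2 eligibility may rest on a chart viral load up to 3 months old, and nothing ties eligibility or analysis to the scheduled baseline draw, so already suppressed entrants can dilute the primary contrast

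*Protocol article*

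**What the plan says.** The Aim 2 Study Sample section sets the target: "We aim to recruit 240 YBLMSM or YBLTW living with HIV who are not virally suppressed". The threshold is "Participants with an HIV-1 viral load>200 copies/mL are eligible to participate in aim 2", and the same section says where the value comes from: "a blood sample for the viral load is obtained (if no recent viral load within 3 months was documented in the medical chart". A qualifying chart result from the previous three months therefore replaces the draw.

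The Aim 2 Study Procedures section then moves on: "After enrollment, participants complete a baseline survey and are randomized (1:1) to 1 of 2 study arms: coach-based MEI or SOC". It mentions no viral load check between enrollment and randomization.

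Table 2, under Data Collection for Aims 2 and 3, has the row "Provide blood for HIV-1 RNA viral load testing (aim 2) or HIV-1 antibody testing (aim 3") with a tick at baseline and at 3, 6 and 12 months, and no exception for a recent chart value. The Abstract's Methods paragraph gives the same specimen schedule.

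The Data Analysis section defines the endpoint on the same marker and the same cut-off: "The primary outcome for aim 2 is durable viral suppression (HIV viral load<200 copies/mL"). It provides for covariate adjustment only if the arms turn out not to be comparable at baseline, and it does not name baseline viral load.

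**The concern.** Eligibility and primary outcome use one marker at one threshold. A dated eligibility value can therefore admit someone who is already in the outcome state. The trial's own schedule treats three months as long enough for suppression status to change, since its first outcome assessment is at month 3. Yet it accepts a three-month-old value as current status at entry. A youth with a chart value above 200 copies/mL eleven weeks ago who has since started or restarted treatment could be below 200 on the day of randomization and still be eligible.

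Such participants are likely to count as suppressed in either arm. They would raise the control rate above the assumed 24% and narrow the difference between arms. The cost is power, and a sample that does not quite match the population named in the aim.

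The eligibility section and Table 2 also need to be reconciled. The first makes the draw conditional; the second schedules it for everyone. Neither says whether the baseline sample is taken before assignment.

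**Working it through.** **Inputs from the article (Sample Size Considerations).** The planned contrast is an average increase over three follow-up visits of "16.0% from 24.0% assumed in the control arm to 40.0% in the coached-based MEI arm (odds ratio, OR 2.03"), with 85% power and about 200 analyzable participants, that is 100 per arm. Attrition reproduces: 240 × 0.85 = 204. The two proportions give an odds ratio of (0.40/0.60)/(0.24/0.76) = 2.11 rather than 2.03. That is a separate matter; the proportions are used below.

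**Assumptions, because the article does not state them.** Two-sided 5% test; a share f suppressed at randomization; a probability s that these participants are suppressed during follow-up.

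**Step 1: reproduce the plan's figure.** Power = Φ(d/SE − 1.96), with SE = √{k[p0(1−p0) + p1(1−p1)]/n}. The factor k allows for averaging three correlated visits.
- With k = 1 (one visit): 0.1824 + 0.2400 = 0.4224; SE = √(0.4224/100) = 0.0650; power = Φ(0.16/0.0650 − 1.96) = 69%. A single-visit comparison does not reach 85%.
- Solving for 85% gives k = 0.675: SE = √(0.675 × 0.4224/100) = 0.0534; 0.16/0.0534 − 1.96 = 1.04; Φ = 85%.
- With k = (1 + 2ρ)/3, this means a within-person correlation ρ of about 0.51, which is plausible. The plan's figure can therefore be matched, but not confirmed from stated inputs.

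**Step 2: dilute, with no benefit in suppressed entrants.** p0 = (1−f)(0.24) + f·s and p1 = (1−f)(0.40) + f·s, with s = 0.90, n = 100 per arm and k = 0.675.

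| f | Control | MEI | Difference | Power |
|---|---|---|---|---|
| 0 | 24.0% | 40.0% | 16.0 points | 85% |
| 5% | 27.3% | 42.5% | 15.2 points | 79% |
| 10% | 30.6% | 45.0% | 14.4 points | 73% |
| 20% | 37.2% | 50.0% | 12.8 points | 61% |

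Example for f = 10%: 0.306 × 0.694 + 0.45 × 0.55 = 0.460; SE = √(0.675 × 0.460/100) = 0.0557; 0.144/0.0557 − 1.96 = 0.62; Φ = 73%. Using s = 0.70 or 0.80 changes power by about 1 point.

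**Step 3: let suppressed entrants benefit too.** Give them the same odds ratio of 2.11, with control-arm suppression s of 70% to 90% (83% to 95% in the MEI arm). Power is then about 81–83% at f = 5%, 76–81% at f = 10% and 68–78% at f = 20%.

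**Step 4: suppose the 24% already includes such entrants.** Hold the control rate at 24% and shrink the difference to 0.16(1−f). At the article's 102 per arm, power is about 78% at f = 10% and 69% at f = 20%.

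**Step 5: restrict to those unsuppressed on a pre-randomization sample.** The rates return to 24% versus 40% with 100(1−f) per arm. Power is about 83%, 81% and 76% at f = 5%, 10% and 20%.

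**The case against.** **The baseline sample is already scheduled.** The Abstract and Table 2 both list it, so the eligibility wording can be read as waiving only the screening draw. This stands. A reader might infer that suppressed entrants could never be identified afterwards, but that follows only if the eligibility section is read as also waiving the baseline specimen. The article does not say so. It also does not say the opposite, or that the sample precedes assignment.

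**A suppressed entrant can still show an effect.** The outcome is durable suppression, and the intervention covers adherence, slips and retention, so preventing rebound is part of what is tested. This stands as well. A reader might infer that every such participant is a certain success whatever the arm; the article does not support that. Step 2 is therefore close to a worst case, and Step 3 shows the milder one.

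**The share f is unknown and may be small.** This stands. For scale, suppose 24% of chart-based entrants had become suppressed by randomization (an assumption borrowed from the planned control rate). Then f = 20% would require 0.20/0.24 = 83% of participants to enter on a chart value; if half did, f would be 12%.

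**Randomization remains valid.** This stands in full: entry precedes allocation, so the rule favors neither arm.

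**A chart window is pragmatic, and sensitivity analyses belong in the SAP.** Aim 2 had enrolled 36 of 240, so excluding or delaying chart-eligible youth has a real cost. The absence of a sensitivity analysis from the article is no fault in itself. The point here is the stated eligibility rule, which does not secure the stated population and does not fit with Table 2.

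**Conclusion.** The concern holds in a limited form. As written, a chart viral load up to three months old can establish eligibility, and no section links eligibility or analysis to the scheduled baseline sample. Some aim 2 participants may therefore already be suppressed at randomization. The consequence is possible dilution and loss of power, not bias toward either arm.

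Its size depends on an f that the article does not give. From the planned 85%, an assumed f of 5% costs about 6 power points if these participants gain nothing and about 2 to 4 if they share the planned odds ratio. An f of 20% costs about 24 points in the first case and about 7 to 17 in the second. All of these figures rest on a two-sided 5% test and on a variance factor chosen to match the stated power. A small f would matter little. Clarification is still worthwhile because the sample is already in the schedule and most of the planned recruitment was still to come.

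**What to change.** 1. In the Aim 2 Study Sample section, state that a recent chart value waives only the screening draw, and that the Table 2 baseline HIV-1 RNA sample is taken from every aim 2 participant before randomization. This reconciles the two places. It costs a sentence and no extra procedure, because Table 2 already lists the draw.
2. Prespecify one use of that sample: either an analysis limited to participants above 200 copies/mL on it, or adjustment of the primary model for baseline suppression status. The subset is defined before assignment, so it remains a randomized comparison, and no enrollment is lost. The restricted analysis drops the participants in whom prevention of rebound could be seen, so it should be reported beside the intention-to-treat result and not replace it.
3. Optionally, require the baseline value to confirm eligibility. This secures the stated population most directly, but fewer youth would be randomized and some would wait for a result. With recruitment this slow, that is a harder choice than steps 1 and 2.

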##### Study Procedures

After enrollment, participants complete a baseline survey and are randomized (1:1) to 1 of 2 study arms: coach-based MEI or SOC. Randomization to the intervention arms is stratified by site; age group, to yield a balanced randomization between younger (aged 15-19 years) and older (aged 20-24 years) age groups; and enrollment site.

##### SOC

Participants randomly assigned to the SOC arm are provided information about and referrals for HIV care and/or prevention. They return to the research setting every 3 months to complete surveys and conversation with assigned study personnel. The focus is on active listening, with no attempts to direct goal setting; screening, brief intervention, and referral to treatment (SBIRT); or motivational interviewing (MI), as discussed below. Personnel are encouraged to refer to local clinical resources, help with participant care navigation, and case management services at each follow-up visit, as needed.

##### Coach-Based MEI

The coached-based MEI is a tailored and enhanced case management strategy that serves as the primary intervention for participants with unsuppressed HIV viral load. Individuals randomized to the coached-based MEI receive weekly telephonic and app-based support and a structured face-to-face meeting every 3 months, augmented by the ongoing implementation of the study’s mobile app. Telephonic and in-person supportive consultations are goal focused and designed to enhance linkage, ART initiation, adherence, and retention in care for MSM diagnosed with HIV [74-76]. The MEI coach is trained in and utilizes Rogerian listening skills, MI, SBIRT for substance use, and personal health goal setting to best support assigned participants [77-81]. It is based on the case management protocol 078 of the HIV Prevention Trials Network (HPTN) [82], emphasizing routine engagement around health behaviors and goals. To meet the needs of youth, the team modified the approach to adapt it for YBLMSM and YBLTW living with HIV and to incorporate the mobile app and MI components.

##### Training and Selection

MEI coaches were hired based on previous work experience in the MSM community, HIV services (eg, outreach, testing, and case management), interest in aiding research, and ability to communicate effectively with the target population. Representation of the MSM, Black, and Latinx communities was encouraged in the job posting process.

MEI coaches received an initial intensive 16-hour training including (1) introduction to study (2 hours); (2) developmental considerations in cognitive and emotional processing in teens and young adults (1 hour); (3) barriers to PrEP uptake, HIV ART adherence, and HIV risk reduction (1 hour); (4) SBIRT, including screening tools for alcohol and drug use, and effective interviewing about substance use (1 hour); (5) discussion on cultural competence and social determinants of health in case management with YBLMSM and YBLTW (1 hour); (6) mobile app and encouraging engagement with participants (1 hour); (7) study fidelity and data recording expectations (2 hours); (8) didactics and group practice on goal setting and health behavior change (1 hour); and (9) MI components on MI spirit, stages of change, core skills (eg, guiding, open-ended questions, affirmations, reflections, and summarizing), collaborative goal setting, *rolling with resistance*, and repeated role-play (6 hours).

MEI coaches receive ongoing training and support during their continued involvement in the study. Bi-weekly, hour-long videoconference supervision on MI application, goal setting, and troubleshooting are provided remotely by a psychologist with expertise in MI training, substance use, and HIV care. In-person, telephonic, and app-based participant communications, successes, and barriers are discussed as well as topical trainings based on coach needs, MI skills, goal setting, and substance use. The MEI coaches routinely audio-record face-to-face visits with participants assigned conditions, and the supervising psychologist provides individualized written and verbal feedback on each recording on the use of MI and goal-setting techniques, as applied to the individual’s circumstances as well as fidelity to the study intervention.

##### Study Intervention

The intervention is administered by a trained MEI coach and includes substance use screening brief interventions and ongoing monitoring throughout the prevention and treatment care cascade [72]. Coaches begin in the initial face-to-face visit with building rapport, explaining the intervention, and identifying personal and health goals. Health goals focus on medication adherence, health care engagement and satisfaction, substance use, and sexual health. Coaches then map out and help the participant prioritize each goal. After the initial question-answer period and establishment of goals, the MEI coach develops an individually tailored plan that is designed to utilize self-determination theory [83] and the Integrated Theory of Health Behavior Change [84] to facilitate the adoption and maintenance of health behaviors. The approach is centered on identified participant goals and values and care engagement, utilizing a card-sort procedure to help prioritize participant goals for each session [77]. Participants who score positive on the CRAFFT (car, relax, alone, forget, friends, and trouble) and Alcohol, Smoking, and Substance Involvement Screening Test are provided with prevention psycho-education around substance use risks [72,73,85]. Participants who score 2 to 3 on the CRAFFT are encouraged to develop a change plan to reduce substance use and scheduled for additional intervention sessions. These cutoffs were used because a CRAFFT score of 2 or higher is optimal for identifying any substance-related problem and an SUD (according to the Diagnostic and Statistical Manual of Mental Disorders, 5th Edition criteria) [86]. Coaches subsequently attempt to link participants who score above 4 to substance use services. Participants who describe sexual risk (eg, condomless anal sex) are also provided psycho-education around sexual risk and PrEP. Coaches help participants develop strategies to avoid substance use and sexual risks in the future.

At the core of the coached-based MEI approach are supportive services such as navigation, adherence counseling, and tailored support for care engagement and treatment adherence for persons living with HIV. This intervention focuses on 3 steps in the support process: MyCare (steps 1 and 2) and MyHealth (step 3). Participants who are living with HIV start with MyCare (step 1) to support the decision to (re-)initiate HIV care. This includes the use of MI to help orient the client toward seeking and initiating care. MyCare (step 1), which is modeled after life steps, a single-session intervention grounded in cognitive-behavioral principles, is at the core of several successful ART adherence interventions [12,87,88]. MyCare (step 2) adds to this evidence-based approach by recognizing that adherence to medications is a personal choice grounded in a variety of behavioral and psychosocial domains. MyHealth (step 3) is based on the premise that a patient engaged in self-management and supportive strategies will feel empowered to take ownership of their own health care needs.

The face-to-face visits consequently address psycho-education about HIV risk, HIV and ART, planning and problem-solving to access and maintain a steady supply of medication, formulating a daily medication schedule, cues for pill-taking, coping with side effects and/or other participant concerns, developing a plan to mitigate side effects and responses to slips in adherence (if applicable), and engaging around condom use and/or limiting sexual risk behaviors. Counseling is tailored to the participants’ specific needs and case management or navigation needed.

Telephonic and app-based check-ins between the MEI coach and participants are conducted to maintain rapport, open communication, review progress on personally identified goals, help troubleshoot challenges that may arise, and provide reminders for upcoming face-to-face visits. The app is used to facilitate communication around medication adherence, medical visit completion, video chat, and bidirectional communication. The MEI coach will determine the participant’s desire for support, and the frequency and schedule of messages. It is the aspirational goal of the study to have the MEI coach have weekly contact with participants; however, this is often not realistic for all participants. For example, some participants will embrace weekly check-ins, others prefer to engage more intermittently, and the remaining participants may experience situational or motivational barriers that may interfere with engagement. MEI coaches may need to utilize MI strategies to explore readiness to engage in telephonic check-ins and study visits and troubleshoot barriers that may arise (Table 1), and re-engagement needs to be pursued by the MEI coach. MEI coaches seek to check-in with participants weekly (at a minimum), and participants are encouraged to attend face-to-face follow-up coach visits at 3, 6, and 12 months. During these face-to-face visits, coaches will work with the participant to review, motivate, and reinforce personal life events, health care engagement, review substance and risk reduction goals, and problem-solve. Using this MI approach, the participant is thus empowered to take the lead with recommendations and guidance from the MEI coach. Permission is sought to audio-record each initial and follow-up study visit for the purpose of assessing study fidelity and providing routine, ongoing feedback to the MEI coach. The recording is at the discretion and informed consent of the participant and the MEI coach. Ad hoc telephonic and in-person support is also provided by the MEI coach, as requested by the participant. An MEI coach, at any time may help, for example, with referral to behavioral health, job resources, community support resources (eg, a food bank), provide supportive listing, or help arrange any requested sexually transmitted infection testing.

**Table 1 table1:** Motivational interviewing approaches to address level of interest in telephonic engagement.

Participant comments	Stage of change	MEI^a^ coach approach
Agreement: “Sure, I wouldn’t mind texting each week.”	Action	Reinforcement, summarize: “Great, I will make sure I will check-in by text each week, or more if wanted by you.”
Barrier: “That would be good, but my phone sometimes cutoffs if I don’t make my bill.”	Determination	Summarize, empower: “I understand. I will try to text each week, and occasionally you may not have cell service. Any ideas of what we could do to stay in touch if your phone loses service?”
Ambivalence: “I’m not sure, I mean I wouldn’t mind, I guess.”	Contemplation	Paraphrase, elicit, affirm: “I hear you might be willing to consider this, and you might not be sure… (Pause...momentary wait...and follow-up if no response)… I have definitely worked with some people who were wary about the check-ins, is there anything about this you might not be thrilled about?”

^a^MEI: mobile-enhanced intervention.

